### Main Outcome Measures

Subjects of the present study will receive 24 treatments after being enrolled, and data of laboratory examinations will be evaluated at 72h and weeks 1, 4, 8, 12, 24, and 48 after intervention (Table 1; Figure 1).

The primary outcome of the present study will be the mean percentage change of the LDL-C level between baseline and weeks 4 and 12 post-treatment (Table 1; Figure 1). The secondary outcome will be MACE (defined as coronary heart disease death, nonfatal myocardial infarction, hospitalization for unstable angina, unplanned coronary revascularization, and stroke) assessed at week 12 and week 48 post-treatment (Table 1; Figure 1). The following issues will also be investigated: (1) the proportion of patients with LDL-C<70mg/dl, <55mg/dl and<40mg/dl during the study period; (2) patients’ quality of life as evaluated with the PROMIS 10 scale at week 12 and week 48 post-treatment; and (3) the percentage change in inflammatory biomarkers including but not limited to high-sensitivity C-reactive protein (hsCRP), interleukin (IL)-1β and IL-6, from baseline to weeks 48 (Table 1; Figure 1). Other biomarkers that exhibit significant difference between the two study arms will be investigated retrospectively after the trial.

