### Study Termination

Patients have the right to withdraw from the proposed study at any time without reason. Such withdrawal will not affect the patients’ rights to receive appropriate medical management in the future. However, researchers will terminate the study for patients having the following situations: poor adherence to the treatments; serious adverse drug reactions; pregnancy; patients refusing to continue participating in the study; lost to follow-up; or other safety reasons.

Excessively high withdrawal rates may lead to unexplained results. Therefore, unnecessary withdrawal should be avoided. Withdrawal reasons should be clarified and registered on the CRF. Researchers should evaluate, judge, and follow up on adverse events that lead to patient withdrawal. Study medications that have been assigned to withdrawing patients cannot be reassigned to other patients. Subjects who quit cannot be replaced. If a subject withdraws before the end of the study, related assessments should be performed for the subject at the end of the study.

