### Statistical Analysis

The primary efficacy analysis will be based on the time from randomization assignment to the first occurrence of any component of MACE. Data will be analyzed using intention-to-treat analysis (ITT) and per protocol (PP) to assess the efficacy and safety of evolocumab in combination with moderate-intensity statin therapy. The superiority of evolocumab will be assessed for all efficacy endpoint. Continuous variables with an approximately normal distribution will be reported with mean±standard deviation (mean±SD), and differences between the two treatment arms will be tested using independent sample t-test. For continuous variables that are not normally distributed, the median and interquartile range (IQR) will be given, and the nonparametric Mann–Whiney U test will be conducted to test for differences between treatment arms. Discrete variables will be reported with counts and percentage for each arm, and differences between arms will be examined using Fisher’s exact test. In order to compare MACE differences, Kaplan–Meier survival curve analysis will be performed, and hazard ratio (HR) and 95% CI will be calculated. Log-rank tests will also be performed to evaluate the differences in significance and verify treatment efficacy.

The ITT population will include all randomized patients and the PP population will include all randomized patients who complete the entire study. Subjects with missing data will be excluded from the corresponding analysis. Logistic regression will be used to analyze differences in the central effect sizes.

Results of the proposed study will be analyzed using SAS 9.2 or higher version (SAS Institute, North Carolina, United States) software. All statistical tests will be two-tailed unless otherwise indicated or presented with a 95% confidence interval (CI), and statistical significance will be established as *p*<0.05.

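### Defining the per-protocol set by study completion keeps every CHD death before week 48 out of the PP MACE analysis, and serious drug reactions that end participation out of PP safety

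*Protocol article*

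**What the plan says.** The Statistical Analysis section defines two populations. For the first, "The ITT population will include all randomized patients". For the second, "the PP population will include all randomized patients who complete the entire study". No eligibility or adherence criterion is attached to the second.

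Both sets are put to the same uses: "Data will be analyzed using intention-to-treat analysis (ITT) and per protocol (PP) to assess the efficacy and safety of evolocumab" in combination with the statin. The section does not say which set governs and does not call PP a sensitivity analysis. It also says that "The primary efficacy analysis will be based on the time from randomization assignment to the first occurrence of any component of MACE", with Kaplan–Meier curves, a hazard ratio and log-rank tests.

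Main Outcome Measures has MACE "defined as coronary heart disease death, nonfatal myocardial infarction, hospitalization for unstable angina, unplanned coronary revascularization, and stroke", assessed at weeks 12 and 48, and LDL-C change assessed at weeks 4 and 12. Follow-up lasts 48 weeks (Patient and Public Involvement). Study Termination lists the grounds on which researchers end a patient's participation. The first is poor adherence, and the list continues with "serious adverse drug reactions; pregnancy; patients refusing to continue participating in the study; lost to follow-up", then other safety reasons.

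**The concern.** A per-protocol set is meant to hold patients who were eligible and treated as planned. This one holds patients who reached the end of follow-up. For three of the planned analyses, reaching the end is either part of the outcome or comes after it.

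- **MACE.** CHD death is the first component listed, and it rules out completion.
- **Safety.** A serious adverse drug reaction is a listed reason for ending participation, so the patients who tolerated treatment worst are the ones taken out.
- **LDL-C.** The endpoint is fully observed by week 12, but the patient must stay 36 weeks more (48 − 12 = 36) to count.

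Because PP stands unranked beside ITT, a PP MACE result that cannot contain a death, or a PP safety table without the patients stopped for drug reactions, could be reported as evidence of efficacy or tolerability.

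**Working it through.** **The rule applied to each kind of patient.** This part needs no event rates.

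| Patient | ITT | PP as written |
|---|---|---|
| CHD death before week 48 | in, counted as MACE | out |
| Non-fatal MACE, stays to week 48 | in, counted | in, counted |
| Non-fatal MACE at week 6, withdraws at week 20 | in, counted | out, including for the week 12 MACE assessment |
| Participation ended for a serious adverse drug reaction | in, data up to exit | out |
| Valid LDL-C at weeks 4 and 12, leaves at week 30 | in | out |
| Ineligible, stays to week 48 | in | in |

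The PP count of CHD deaths before week 48 is therefore 0 by definition. So is the PP count of patients whose participation ended for a serious adverse drug reaction.

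**Size of the set.** The only figure in the document that bears on this is the 20% drop-out allowance in Sample Size Calculation. It reproduces: 193 / (1 − 0.20) = 241.25, rounded up to 242 per arm, and 2 × 242 = 484. If the same 20% applied to completion at week 48 for the 500 patients to be enrolled, 0.20 × 500 = 100 would leave PP and 400 (200 per arm) would remain. That is an assumption, because the allowance belongs to a calculation on week 4 LDL-C and no 48-week completion rate is given.

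**Deaths affected.** No mortality figure is given. At an assumed CHD mortality of 1% to 4% over 48 weeks, 0.01 × 500 = 5 to 0.04 × 500 = 20 patients.

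**Effect on the comparison (illustration, all rates assumed).** Take 250 per arm and 8% non-fatal MACE in each arm (20 patients), none of whom die, with death the only reason for not completing.

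- ITT risk = (deaths + 20) / 250
- PP risk = 20 / (250 − deaths)

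| CHD death, arm A v arm B | ITT risk | ITT RR | PP risk | PP RR |
|---|---|---|---|---|
| 3% v 2% (7.5 v 5 expected) | 27.5/250 = 11.0% v 25/250 = 10.0% | 1.10 | 20/242.5 = 8.2% v 20/245 = 8.2% | 1.01 |
| 9% v 6% (22.5 v 15 expected) | 42.5/250 = 17.0% v 35/250 = 14.0% | 1.21 | 20/227.5 = 8.8% v 20/235 = 8.5% | 1.03 |

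The arms are unlabelled on purpose. If A is evolocumab, PP hides harm; if A is statin-only, PP hides benefit. Here the mortality difference all but disappears in either direction.

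**Safety.** If an assumed 1% to 10% of an arm were stopped for drug reactions, 2.5 to 25 of 250 patients would be in the ITT safety data and none in PP safety.

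**The case against.** Several points stand against reading more into this.

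- **The trial does not lose its deaths or drug reactions.** A reader might infer that the definition strips all deaths from the MACE results and all toxicity cases from the safety results. The document does not support that. ITT holds all randomized patients. Safety Evaluation summarizes adverse events by randomized group and lists death among the serious ones. Study Termination asks for follow-up of adverse events that lead to withdrawal. All of this stands.
- **The bias need not favour evolocumab.** A reader might infer that PP flatters the study drug by construction. The fatal component does fall to zero in both arms, which lowers the absolute rate. The between-arm effect depends on where deaths fall, and in the illustration it moves towards no difference. Event-free leavers are removed too, and that pushes the absolute rate the other way. For safety, reactions to evolocumab can end participation only in the arm that receives it, which suggests a direction, but the document gives no rates.
- **Completion carries some adherence content.** Poor adherence is itself a ground for ending participation, so a known poor adherer should not become a completer. This stands, but it does nothing for ineligible completers or for deaths.
- **The populations may be settled later.** Data Collection and Management has the trial team review the data and finalize the analysis populations, and an article may leave deviation criteria to the full protocol or analysis plan. The absence of a detailed deviation list is therefore not the complaint. What is printed is a definite rule that selects on the outcome, and a later review does not cure it. In an open-label trial, settling the set after seeing data is also weaker protection than fixing it in advance.
- **ITT would normally carry the conclusion in a superiority trial.** It would, but the section gives PP equal standing.

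**Conclusion.** The definition is wrong as written, within the PP analyses only. PP MACE cannot contain a CHD death before week 48, PP safety omits patients whose participation ended for serious adverse drug reactions, and PP LDL-C discards patients for events after the endpoint was measured. These follow from the text and need no rates. They rest on the plain reading that a patient who dies or whose participation is ended has not completed the entire study. Study Termination asks for end-of-study assessments of withdrawn patients, but nothing says that this makes them completers.

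The numbers rest on assumptions: 5 to 20 deaths on 1% to 4% CHD mortality, about 100 patients outside PP on a 20% allowance carried over to week 48, and the relative risks on invented event rates. ITT and the safety summary by randomized group are not touched by this definition, and no sample-size figure changes. How much weight PP MACE would carry also depends on whether MACE is primary, as Statistical Analysis has it, or secondary, as Main Outcome Measures has it; that conflict is a separate matter.

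Requiring completion also gains nothing for MACE, since the planned Kaplan–Meier and log-rank methods already handle early exit by censoring.

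**What to change.** Replace the PP definition in Statistical Analysis with one that says:

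1. PP consists of randomized patients without a pre-specified major protocol deviation: eligibility breach, assigned treatment not received, or adherence below a level the sponsor sets in advance.
2. Deviations are judged only up to the endpoint's time point: week 4 or week 12 for LDL-C, and the event or censoring time for MACE.
3. Death, MACE or stopping for an adverse event never excludes a patient from PP.
4. PP is a sensitivity analysis to ITT.
5. Safety conclusions rest on all randomized or all treated patients, not on completers. The randomized-group summary already in Safety Evaluation can serve.

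The cost is a few sentences and a deviation listing fixed before database lock. No sample size, visit or data item changes.

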### Safety Evaluation

For safety outcome analysis, missing data will not be imputed. Adverse events (AEs) will be recorded and summarized using descriptive statistics. Tolerability of study drug will be monitored and evaluated throughout the study period *via* regular medical examination and laboratory tests. For analyses of clinical endpoints, incidence of AEs and/or serious adverse events (SAEs) will be summarized for each randomized treatment group. Serious adverse events include cardiovascular events (death, fatal or non-fatal MI, coronary revascularization, hospitalization for recurrent ACS, hospitalization for heart failure, stroke, transient ischemic attack), muscle-related adverse events, neurocognitive impairments, incident diabetes; adverse events of special interest include allergies, injection-site reactions, or any other clinical abnormalities. If unexpected or SAE occur, the researchers or staff will fill out the SAE Report Form and notify the Ethics Committee and the State Food and Drug Administration (SFDA) as well as the pharmacological authorities.

Possible intervention-related complications will be recorded at 72h, and weeks 1, 4, 8, 12, 24, and 48 after intervention, including: dissection, acute thrombosis, coronary perforation, puncture site complications, allergic reactions, vasovagal response, perioperative myocardial infarction, cerebrovascular events, and hypotension.

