### Sample Size Calculation

This is a superiority trial, and the sample size calculation is based on the primary efficacy endpoint, namely the percentage of change in LDL-C levels from baseline to week 4 after randomization. In order to have 90% power to detect clinically meaningful differences in treatment effects with a one-sided significance level of 5% (α=0.05), a sample size of 193 patients is required for each treatment arm. Assuming that the drop-out rate is 20%, this study aims to enroll approximately 484 patients, with 242 patients in the evolocumab plus statin arm and 242 in the statin-only arm. Therefore, the proposed study is expected to enroll a total of 500 patients with acute phase ACS, with 250 patients in each treatment arm.

The number of patients enrolled from each hospital is based on the bed size of each hospital. The Tianjin Chest Hospital plans to enroll 220 patients, and the remaining seven hospitals each will enroll 40 patients.

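### The ITT set includes everyone randomised, but the plan's only efficacy missing-data rule excludes patients without the value, so LDL-C becomes an available-case comparison open to treatment-related loss

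*Protocol article*

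**What the plan says.** The Statistical Analysis section defines its two populations in one sentence: "The ITT population will include all randomized patients and the PP population will include all randomized patients who complete the entire study". The sentence after it gives the only missing-data rule for efficacy: "Subjects with missing data will be excluded from the corresponding analysis". Continuous endpoints are compared by t-test or Mann–Whitney test, discrete ones by Fisher's exact test, and MACE by Kaplan–Meier curves, a log-rank test and a hazard ratio. For safety the rule is stated separately: "For safety outcome analysis, missing data will not be imputed".

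The Study Termination section says that "researchers will terminate the study for patients having the following situations: poor adherence to the treatments; serious adverse drug reactions; pregnancy", and goes on to refusal, loss to follow-up and other safety reasons. For patients who withdraw early it asks for assessments, not further specified, when the study ends.

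The Sample Size Calculation section works from LDL-C change at week 4: "Assuming that the drop-out rate is 20%, this study aims to enroll approximately 484 patients". The Main Outcome Measures section makes percentage change in LDL-C at weeks 4 and 12 the primary outcome. It also lists MACE at weeks 12 and 48 and the proportions of patients below three LDL-C thresholds.

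**The concern.** This is a stated rule, not detail left for an analysis plan. One sentence promises analysis of everyone randomised. The next removes, endpoint by endpoint, whoever lacks the value. An analysis plan that kept all randomised patients in the LDL-C comparison would have to contradict the protocol.

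The rule matters because the protocol helps to create the missing values. Poor adherence and serious drug reactions arise after randomisation and are related to treatment. The trial is open-label and only one arm receives injections, so removal may occur at different rates, or for different reasons, in the two arms. If so, the patients with week-4 and week-12 LDL-C are no longer the groups that randomisation made comparable, and the t-test on observed values offers nothing to offset that. What is at stake is the size of the reported LDL-C effect, and the use of ITT as a check that is independent of the per-protocol analysis.

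**Working it through.** **1. The plan's own figure.** Inputs from Sample Size Calculation: 193 evaluable patients per arm and 20% drop-out.

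- Per arm: 193 / (1 − 0.20) = 241.25, rounded up to 242. Total: 2 × 242 = 484. This matches the plan.
- Planned loss: 484 − 2 × 193 = 98 patients. At the rounded enrolment of 500: 0.20 × 500 = 100, leaving 200 per arm.

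The plan therefore expects to analyse week-4 LDL-C only in patients who have the value. The 193 cannot itself be rederived, because no effect size or SD is given.

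**2. Power is not the problem.** Back-solving 193 per arm at 90% power and one-sided 5% gives a standardised difference of (1.645 + 1.282) × √(2/193) = 0.298. At that difference, 200 per arm still has 90.9% power one-sided. The issue is bias.

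**3. Which analyses the rule touches.**

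| Analysis | Effect of the exclusion rule |
|---|---|
| LDL-C % change, weeks 4 and 12 | Patient without that visit's value drops out of that comparison |
| Proportion below LDL-C thresholds | Same |
| MACE status at week 12 or 48, if tested as a proportion | Patient with unknown status drops out |
| Time to first MACE | Unclear: the methods normally censor, but no exception to the rule is written |

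**4. Whether the missing values could be recovered.** Table 1 schedules lipids at screening and at weeks 1, 4, 12, 24 and 48. For a patient taken out before week 4, Study Termination provides only the end-of-study assessment, which supplies neither primary time point.

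**5. Illustration of size.** These are assumptions, not figures from the document: a fraction *m* of the evolocumab arm is missing, all because treatment stopped; those patients retain a fraction *r* of the effect; control-arm missingness is neutral. Then

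- effect in all randomised ÷ available-case effect = (1 − m) + m × r
- overstatement = 1 / [(1 − m) + m × r] − 1

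| m | r | ratio | overstatement |
|---|---|---|---|
| 5% | 0.5 | 0.975 | 2.6% |
| 5% | 0 | 0.950 | 5.3% |
| 10% | 0.5 | 0.950 | 5.3% |
| 10% | 0 | 0.900 | 11.1% |
| 20% | 0.5 | 0.900 | 11.1% |
| 20% | 0 | 0.800 | 25.0% |

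Even in the last row, 80% of the available-case effect remains.

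**The case against.** **Completer analysis.** A reader might infer that ITT collapses into a completer analysis. It does not. The exclusion applies to the analysis concerned, so a patient who leaves at week 20 still counts at weeks 4 and 12. The completer set is the separately defined per-protocol population. For the same reason, if drop-out is spread over 48 weeks, loss at week 4 may be well under 20%, although the sample size applies 20% to that endpoint.

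**MACE.** A reader might also infer that patients with incomplete follow-up are deleted from the MACE survival analysis. That is the literal reading of a general sentence, but not the only one. Kaplan–Meier, log-rank and hazard-ratio methods ordinarily censor such patients, and someone with observed time at risk need not count as having missing data. What stands is that the text should say so.

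**Direction and size.** It is tempting to state that the effect will be overstated by a given number of points. The document gives no on-treatment or off-treatment LDL-C response, no SD and no drop-out by arm. The termination rule covers both arms, so dropping poorly adherent statin-only patients could overstate the control fall and partly offset the bias. Some reasons for leaving, such as loss to follow-up or refusal, need not mean that the drug was stopped for lack of adherence or tolerance. Differential loss is plausible, not shown.

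**Consequence.** The abstract cites an LDL-C reduction with evolocumab of about 60%. Against an effect of that order, the distortion illustrated above is unlikely to change the superiority conclusion.

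**Safeguards.** The Study Termination section does ask that unnecessary withdrawal be avoided, that reasons be recorded and that withdrawn patients be assessed at the end. This helps, but it does not secure week-4 or week-12 LDL-C.

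None of these points removes the conflict between the ITT definition and the exclusion rule for visit-based endpoints.

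**Conclusion.** The point holds for endpoints read at a visit. As written, the ITT comparison of LDL-C at weeks 4 and 12 is an available-case comparison, and the protocol's own termination rule allows patients to be lost from it for reasons that may be related to treatment. Planned loss is 98 of 484 (100 of 500), as an upper planning figure for week 4.

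The bias cannot be sized or signed from the document. Under the labelled assumptions (5–20% missing in the evolocumab arm because treatment stopped, 0–50% of the effect retained, neutral loss in control) the overstatement runs from about 3% to 25%. That would distort the estimate without being likely to reverse LDL-C superiority. For time to first MACE, the document supports a request for clarification only. This should be fixed, but it does not by itself invalidate the trial.

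**What to change.** 1. **Study Termination.** For data-collection purposes, distinguish stopping study drug from leaving the study. Continue the blood draws and event follow-up already scheduled in Table 1 unless the patient withdraws consent. This concerns data only and sets no rule on when treatment stops. It is the key step, because values never collected cannot be recovered at analysis.
2. **Statistical Analysis.** Replace the exclusion sentence. Analyse all randomised patients by assigned arm, using every observed LDL-C value including those after study drug stops, in a likelihood-based repeated-measures model or with multiple imputation. Add a control-based sensitivity analysis for values not missing at random. A missing-at-random model alone is not enough: it predicts absent values from similar observed patients, who are largely still on treatment, and would not generally recover a loss of effect after stopping.
3. **MACE.** State that the exclusion rule does not apply to time to first MACE, and that every randomised patient is included and, if no event has occurred, censored at the last contact known to be event-free.

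The cost is a wording change, some extra follow-up effort at visits that already exist, and possibly a less favourable LDL-C estimate.
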